##### Hypothesis 1a

Compared to sham, real treatment will lead to greater reduction in TS from baseline (week 0) to end of week 4.

##### Planned analysis

This hypothesis will be tested using the two-tailed, two-sample *t* test, comparing the change in TS from baseline to week 4 between the real and sham arms.

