**Methods:**

We present the aims and methods of a placebo-controlled, participant-blinded and assessor-blinded mechanistic study. Adult patients with CLBP will be randomized to receiving 16 sessions of real (active) or sham (placebo) EA over the course of 8 weeks. The primary pain regulatory measure for which the study was powered is temporal summation (TS), which approximates ascending pain facilitation. Conditioned pain modulation (CPM), representing a descending pain modulatory pathway, will be our secondary pain regulatory measure. The primary psychological measure is expectations of benefit, and the secondary psychological measures are pain catastrophizing and self-efficacy in managing pain. Main clinical outcomes are back pain bothersomeness on a 0–100 visual analog scale (primary), Roland Morris Disability Questionnaire (secondary), and relevant items from the National Institutes of Health (NIH) Patient-Reported Outcome Measures Information System (secondary). We hypothesize that compared to sham, real EA will lead to greater reduction in TS after 8 treatment sessions (4 weeks); and that reduction in TS (and secondarily, increase in CPM) after 8 treatment sessions will mediate reduction in back pain bothersomeness from baseline to week 10 (clinical response) to EA. We also hypothesize that the three psychological factors are moderators of clinical response. With 100 treatment completers, the study is designed to have 80% power to detect a medium-sized between-group effect (*d* = 0.5) on temporal summation.

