#### Sample size

We computed the sample size based on detecting differential changes in TS, the primary mediator. A small pilot study conducted in our laboratory suggested an average change of 10–25 points on the 100-point VAS with a standard deviation of 12 in TS following acupuncture. Prior studies suggest no treatment effect in controls receiving sham acupuncture [35]. However, given the imprecision of the pilot study estimates of effect sizes, we have elected to power the study to detect a medium-sized effect (*d* = 0.56) with 50 subjects in each arm, using the two-tailed test with alpha = 0.05 and beta = 0.8. If the point estimates from the pilot prove to be correct, this project will be very well-powered (98% power) to detect a large effect (*d* = 0.833). To account for attrition of about 20%, we plan to enroll about 120 study participants.

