#### Randomization, allocation concealment and blinding

We will randomize eligible participants to either the real or the sham intervention arm using a biased coin algorithm [56], which is an adaptive randomization process that aims to equalize the baseline pain level between the two groups. Given the influence of baseline pain level on clinical outcomes of pain studies [57], and our limited sample size, we decided to focus on equalizing levels of baseline pain severity, and not to equalize other factors, such as gender and age, which had less impact on the final outcome in past research [58, 59]. Each participant will be classified as having more or less extreme baseline pain (using 7/10 as a pain severity cutoff score). The algorithm will shift the randomization from a 50/50% chance of sending a participant with extreme pain into either treatment arm to having a 40/60% chance of assigning the participant with extreme pain into the arm that has more participants with extreme pain.

Participants will be randomized by the research staff who screen and enroll the participant but do not conduct baseline, mid-point, or post-treatment assessments. Specifically, once a participant is enrolled, the staff will enter the participant’s ID and pain severity into a randomization program written in R-3.4.3. The program will return the randomization assignment (i.e., allocation). A research staff member, who is not involved in the assessment of outcome, will then inform the acupuncturist via secure email, about the treatment allocation. The acupuncturist will email back, acknowledging receipt of the participant ID and allocation and will then initiate contact with the participant to schedule the first intervention session.

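### Hypothesis 1a is tested by an unadjusted t test on TS change; ANCOVA on baseline TS and the randomization's pain stratum would be at least as precise, with a gain that depends on an unstated correlation

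*Protocol article*

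**What the plan says.** Under Statistical methods, the planned analysis for hypothesis 1a is a "two-tailed, two-sample *t* test, comparing the change in TS from baseline to week 4 between the real and sham arms". It names no covariate. The mixed models for hypothesis 1b contain treatment arm, then arm, TS reduction and their interaction. The model for hypothesis 2 contains expectation, arm and their interaction. Baseline pain severity appears in none of them.

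The randomization section describes "an adaptive randomization process that aims to equalize the baseline pain level between the two groups", with participants classified at 7/10. It justifies this by the influence of baseline pain on clinical outcomes in pain studies.

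The sample size section powers the trial for a "medium-sized effect (*d* = 0.56) with 50 subjects in each arm", "using the two-tailed test with alpha = 0.05 and beta = 0.8" (0.8 is evidently the power), and calls the trial "very well-powered (98% power) to detect a large effect (*d* = 0.833") if the pilot estimates hold. The abstract gives a different effect size: "With 100 treatment completers, the study is designed to have 80% power to detect a medium-sized between-group effect (*d* = 0.5").

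**The concern.** TS at baseline is measured on every participant in the primary analysis set. A change score subtracts it with a coefficient of 1, whereas ANCOVA estimates the coefficient from the data. Unless the best coefficient is close to 1, the change score carries extra variance. Any chance imbalance in baseline TS then also feeds regression to the mean into the arm comparison. The primary set consists of treatment completers, so randomization does not fully guarantee balance in the participants analysed.

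The pain factor raises a second, smaller issue. If a factor is balanced by design and is prognostic, leaving it out of the model means that the standard error takes no credit for the balance.

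What is at stake is precision in the one comparison that determined the sample size.

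**Working it through.** **Inputs from the article.** 50 per arm; two-sided alpha 0.05; d = 0.56 (sample size section) or d = 0.5 (abstract); pilot SD 12 with a change of at least 10 points, so 10/12 = 0.833. I read d in SDs of the change score, because the sample size section refers to differential changes in TS.

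**Assumed, not in the article.** The baseline to week 4 correlation rho, and equal SDs at the two times.

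**Step 1: the plan's own figures.** Power of the two-sample t test (noncentral t, 98 df, noncentrality d × √(50/2)):

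- d = 0.56: 79.2% (80.0% by the normal approximation). This reproduces the stated 80%.
- d = 0.833: 98.5%. This reproduces the stated 98%.
- d = 0.5: 69.7%. This does not reproduce the abstract's 80%, which would need about 64 per arm.

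**Step 2: variance of the two analyses.** Let s0 and s1 be the SDs at baseline and week 4.

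- Var(change) = s0² + s1² − 2·rho·s0·s1
- Var(ANCOVA) = s1²(1 − rho²)
- Difference = (s0 − rho·s1)², which is never negative.

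With s0 = s1 = s, these become 2s²(1 − rho) and s²(1 − rho²), and the ratio of ANCOVA to change score is (1 + rho)/2.

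**Step 3: power with ANCOVA on baseline TS.** The effective effect size is d/√((1 + rho)/2), with 97 df. For example, at rho = 0.5 and d = 0.5 it is 0.5/√0.75 = 0.577.

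| rho | variance ratio | power, d = 0.56 (t test 79.2%) | power, d = 0.5 (t test 69.7%) |
|---|---|---|---|
| 0.3 | 0.65 | 93.0% | 86.7% |
| 0.5 | 0.75 | 89.3% | 81.5% |
| 0.7 | 0.85 | 85.2% | 76.6% |
| 0.8 | 0.90 | 83.2% | 74.2% |
| 0.9 | 0.95 | 81.2% | 71.9% |

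At d = 0.5 the gap is 80 − 69.7 = 10.3 points. ANCOVA closes all of it if rho is about 0.56 or lower, and at least half if rho is about 0.77 or lower. At rho 0.8 it closes (74.2 − 69.7)/10.3 = 44%.

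**Step 4: sensitivity to the equal-SD assumption.** Take rho = 0.7, s0 = 1 and s1 = 1.3. Then Var(change) = 1 + 1.69 − 1.82 = 0.870 and Var(ANCOVA) = 1.69 × 0.51 = 0.862, a gain of about 1%. A week 4 SD below the baseline SD would give a larger gain than the table shows.

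**Step 5: the pain stratum.** A simulation of 8,000 runs per setting assumed that 30% of participants are in the extreme-pain stratum, split evenly between arms. With an assumed stratum shift of 0.5 change-SD in TS, adding the stratum to the ANCOVA gains about 2 points of power. Under the null in the same setting, the unadjusted t test has a type I error of about 0.039 to 0.046, so it is slightly conservative. With no stratum effect on TS, adding the stratum gains nothing.

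**The case against.** The strongest reply is that nothing here is an error. The t test on change is valid under randomization, answers hypothesis 1a as worded and matches the basis of the sample size. At d = 0.56 design and analysis agree. All of that stands. ANCOVA answers the same question, however: with baseline TS in the model, the arm effect is the same whether the outcome is week 4 TS or the change.

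A reader might go further than the article allows in four ways.

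- *Baseline TS is ignored.* It is not; it enters with a fixed coefficient.
- *The choice of test leaves the trial underpowered.* The gap to 80% exists only against the abstract's d = 0.5. That is a conflict between two stated effect sizes, not a fault of the test.
- *ANCOVA would restore most or all of that power.* This depends on rho and the SDs. Above a rho of about 0.77, less than half of the gap closes.
- *Omitting the pain factor risks false positives.* In the simulation it made the test slightly conservative.

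The stratum argument is weak for TS: the randomization section links baseline pain to clinical outcomes, not to TS, and its 40/60 coin gives only partial balance. It is stronger for the bothersomeness models.

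A separate analysis plan may add covariates. But the article specifies this test and lists the terms of its models, so the choice can be assessed as published.

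**Conclusion.** The point holds as one of efficiency and consistency. The planned test is valid but gives up precision that data already collected could supply, and the factor used in the randomization appears in no planned model. With equal SDs and rho between 0.3 and 0.8, ANCOVA adds about 4 to 14 points of power at d = 0.56 (79.2% to between 83.2% and 93.0%) and about 4 to 17 points at d = 0.5 (69.7% to between 74.2% and 86.7%). Because the article gives neither rho nor the SDs, these figures are illustrations and not estimates; the true gain could be close to zero or larger. The gain from the pain stratum in the TS analysis is probably small.

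**What to change.** Before unblinding:

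1. Specify ANCOVA of week 4 TS on arm, baseline TS and baseline pain stratum (7/10 cutoff), two-sided 5%, as the primary test of hypothesis 1a.
2. Add the pain stratum to the mixed models for hypotheses 1b and 2, where the randomization section's rationale applies most directly.
3. Keep the t test on change as a sensitivity analysis.
4. Reconcile d = 0.5 in the abstract with d = 0.56 in the sample size section, and state the rho and SDs assumed for any power quoted for the adjusted analysis.

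The cost is a documented amendment and one or two degrees of freedom. No further participants or measurements are needed. The article expected recruitment to end by 31 December 2018, so the amendment should be dated and shown to precede unblinding.

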##### Hypothesis 1b

Reduction in TS from baseline to week 4 will mediate reduction in weekly back pain bothersomeness scores over the course of treatment (from baseline to post-treatment, around week 10).

##### Planned analysis

We will use a McArthur mediation analysis strategy [60] to test this hypothesis. We will first examine if there is a significant treatment effect on the clinical outcome, testing a mixed effect model, with weekly back pain bothersomeness scores as the dependent variable and treatment assignment as the independent variable. The subject-specific intercept will be included to account for within-patient correlation. We will then test a second mixed effects model, with the longitudinally measured back pain bothersomeness scores as the independent variable. Treatment arm, reduction in TS from baseline to week 4, and their interaction will be the independent variables. A significant main effect for change in TS or an interaction between change in TS and treatment arm will be interpreted as evidence of mediation.

##### Hypothesis 2

Participants’ expectations of benefits will predict reduction in back pain bothersomeness scores during the treatment period (week 0 to week 10).

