#### Primary measures

Temporal summation (TS) - ascending pain facilitatory mechanism (primary mediator): we will use an individualized thermal TS protocol, measured on the back and the hand of each participant [50]. Through a unique participant training process and steps that aim to optimize TS by adjusting the stimulus and baseline temperatures, our method minimizes floor and ceiling effects due to variability in heat sensitivity and enables the capture of TS in a broad range of individuals [51]. This protocol delivers a series of 10 individually adjusted, supra-threshold heat pulses (0.5 s duration, given every 2 s) to the participant’s palm. TS is estimated as the difference between the rating of the second pain from the first pulse from that of the most painful pulse. We will measure TS at baseline (pretreatment measurement), during the treatment period (between the 8th and 9th treatment session), and post treatment.

Expectation of benefit - psychological mechanism (primary moderator): the Stanford Expectation of Treatment Scale (SETS) is a validated measure that assesses both positive and negative expectancies. It has a total of 6 questions (3 assessing positive and 3 negative expectations) and all questions are answered by a 7-point Likert scale scored from 1 to 7. The Cronbach’s alpha was 0.81–0.88 for positive expectancies and 0.81–0.86 for negative expectancies measured by the SETS. Participants will complete SETS both before and after the first treatment session.

Self-reported back pain bothersomeness - primary clinical outcome: participants will rate weekly back pain bothersomeness using a visual analog (VAS) 0–100 scale, where 0 is no pain and 100 is the worst pain imaginable. The back pain bothersomeness scale is specific to back pain and has been successfully used by researchers in other clinical trials [10, 52]. This measure will be collected weekly from baseline (week 0) to the post-treatment visit (around week 10).

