##### Planned analysis

This hypothesis will be tested using a mixed effects regression analysis with weekly measured back pain bothersomeness scores as the dependent variable and expectation, treatment assignment, and their interaction as independent variables.

Hypotheses for aim 3 will be tested using the same analytic plan, replacing primary measures with secondary measures.

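### The models for Hypotheses 1b and 2 contain no week term and so do not test reduction; if a linear change term is added under the stated subject intercept alone, its false-positive rate could exceed 5%.

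*Protocol article*

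**What the plan says.** Under Statistical methods, Hypothesis 1b states that reduction in TS from baseline to week 4 "will mediate reduction in weekly back pain bothersomeness scores over the course of treatment". Hypothesis 2 states that expectations predict reduction in the same score over weeks 0 to 10. Under Primary measures, the score is collected weekly from week 0 to the visit around week 10, which makes 11 ratings per participant.

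The models are:

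- **Hypothesis 1b, first model:** a mixed model "with weekly back pain bothersomeness scores as the dependent variable and treatment assignment as the independent variable". For the repeated ratings, "The subject-specific intercept will be included to account for within-patient correlation".
- **Hypothesis 1b, second model:** "Treatment arm, reduction in TS from baseline to week 4, and their interaction will be the independent variables". A significant TS-change main effect or TS-change-by-arm interaction is to be read as evidence of mediation.
- **Hypothesis 2:** "This hypothesis will be tested using a mixed effects regression analysis with weekly measured back pain bothersomeness scores as the dependent variable", with "expectation, treatment assignment, and their interaction as independent variables". No random effects are named.

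No model lists week or an interaction with week. The article mentions no random slope and no residual correlation.

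**The concern.** There are two linked problems.

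First, the hypotheses are about change, but every listed predictor is constant within a participant. With no week in the model, its coefficient describes the average of that participant's weekly scores. For arm, randomisation makes this a valid, though diluted, comparison. TS change and expectation are not randomised. Participants with high expectation could have lower scores from week 0 onwards and improve no more than others, and the listed test could still be significant.

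Second, the natural repair is to add week and predictor-by-week terms. A subject intercept alone assumes that weeks 0 and 10 are as strongly correlated as weeks 9 and 10, and that participants with the same predictors follow parallel courses. If participants improve at different rates, or if neighbouring weeks are more alike than distant ones, the model treats that structure as independent weekly noise. The standard error of a linear change term is then too small. Repairing only the fixed effects would therefore introduce an error that the current terms do not have, and the mediation and moderation conclusions would rest on it.

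**Working it through.** **The plan's own figures.** The article states no error rate for the mixed models. Its Sample size section works "with 50 subjects in each arm, using the two-tailed test with alpha = 0.05 and beta = 0.8" (the 0.8 read as power), for TS change. With d = 0.56, power = Φ(d√(n/2) − 1.96) = Φ(0.56 × 5 − 1.96) = Φ(0.84) = 80.0%. With d = 0.833, it is Φ(2.205) = 98.6%. Both agree with the article. From this section only n = 50 per arm and two-sided α = 0.05 are carried forward.

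**Inputs.** From the documents: 100 participants, T = 11 weekly ratings, α = 0.05. Assumed, because the documents give no values: residual SD σ = 12, slope SD σ_b from 0 to 2 points per week or AR(1) residual correlation ρ, and no true effect.

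**Formulas for a linear arm-by-week term.** Centre week at 5, so that Σt² = 2(1 + 4 + 9 + 16 + 25) = 110.

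- True variance of one person's fitted slope: V = σ_b² + σ²/110.
- Residual mean square under an intercept-only model: s² = [1000σ² + 11000σ_b² − 2(110σ_b² + σ²)]/998 ≈ σ² + 10.8σ_b².
- Variance the model believes: M = s²/110.
- Rejection rate: 2[1 − Φ(1.96/√(V/M))].

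| σ_b (points/week) | V | M | √(V/M) | False-positive rate |
|---|---|---|---|---|
| 0 | 1.309 | 1.309 | 1.000 | 5.0% |
| 0.5 | 1.559 | 1.334 | 1.081 | 7.0% |
| 1 | 2.309 | 1.407 | 1.281 | 12.6% |
| 1.5 | 3.559 | 1.530 | 1.525 | 19.9% |
| 2 | 5.309 | 1.702 | 1.766 | 26.7% |

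**Autocorrelation, no slope variation.** The same comparison of true with model-based variance gives √(V/M) = 1.287 at ρ = 0.3 (12.8%) and 1.541 at ρ = 0.5 (20.3%).

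**Wider range.** With ρ = 0.9 the rate is 38.7%. When the SD of the week 0-10 change due to slopes is three times the residual SD, it is 40.4%. On that scale, σ_b of 1 and 2 are ratios of 10/12 = 0.83 and 20/12 = 1.67.

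**Simulation, 6,000 trials per scenario.** Scenarios were AR(1) ρ from 0 to 0.8, or slope ratios from 0.5 to 2.

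| Test | Rejection rate under no effect |
|---|---|
| Arm main effect, as listed in the plan | 4.8-5.7% |
| Arm by linear week, intercept only | 5.0-34.6% |
| Arm by week 10 versus week 0, intercept only | 4.6-13.4% (AR(1)); 6.0-16.9% (slopes) |
| Arm by weeks 1-10 versus week 0, intercept only | 5.0-10.4% |
| Person-level slope t test | 4.5-5.6% |

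A continuous predictor, such as TS change or expectation, behaves the same way (intercept SD 15, residual SD 12). With slope SD 1 and 2, the predictor-by-week test rejects in 12.8% and 27.1% of trials, the average-level test in 4.8% and 5.2%, and the person-level slope test in 4.7% and 5.1%.

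**The case against.** The strongest reply is that the inflated test is not in the plan. The article names its deciding terms for mediation, and they are person-level. A subject intercept handles those correctly, as the simulation confirms. This stands. A reader might infer that the listed tests of arm, TS change or expectation carry a false-positive rate of 12-27%, or that the interval for the listed arm effect is too narrow. The documents do not support either inference.

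The text also says that the intercept will be included, not that nothing else will be. The sentence follows the first Hypothesis 1b model, and the Hypothesis 2 plan names no random effects, so carrying the intercept over to Hypothesis 2 is an inference. A fuller analysis plan may say more, and silence on covariance details would not by itself be a finding.

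Finally, 12-27% comes from chosen variances and one form of change test. Small slope variation gives 5-7%, and contrasts against week 0 are inflated less. This stands too, so the range has to be given as conditional.

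The reply does not remove the mismatch between hypotheses about reduction and stated models with no week term. Nor does it make the one stated allowance for correlation adequate for the linear change test that would close that gap.

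**Conclusion.** The point holds in conditional form. As listed, the models keep about 5% type I error but test average level, so they do not answer Hypotheses 1b and 2 as worded. If reduction is tested by a linear predictor-by-week term with a subject intercept alone, the false-positive rate could be about 12-27% for slope SDs of 1-2 points per week with residual SD 12, or about 13-20% for autocorrelation of 0.3-0.5. These are moderate assumptions, not values from the documents. The possible range is 5% (no slope variation or autocorrelation) to about 40%, and about 5-17% for contrasts against week 0. Modelling each person's slope brings the rate back to about 5% in every scenario examined.

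**What to change.** In the models for Hypotheses 1b and 2, add week and the predictor-by-week terms that express reduction: arm by week, TS change by week, expectation by week, and their three-way terms with arm where the plan has an interaction. State that these are the deciding terms.

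In the same sentence, specify a subject-specific random slope for week with an unstructured intercept-slope covariance. An unstructured or AR(1) residual covariance with small-sample degrees of freedom is an alternative. If the model does not converge, fall back to person-level slopes or change scores. The fixed effects and the covariance should be changed together, because changing only the first would bring in the inflation shown above.

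The cost is a short revision of the two planned-analysis paragraphs and no new data. The confidence intervals for the change terms will be wider than under an intercept alone, and correct.

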##### Clinical impact

This clinical trial aims to delineate pain regulatory and psychological mechanisms of real (active) versus sham (placebo) EA in treating CLBP. The primary mechanisms investigated in this study are ascending pain facilitation estimated by TS, a specific measure from quantitative sensory testing, and expectations of benefit from the intervention, a psychological measure. The primary clinical outcome in this mechanistic study is back pain bothersomeness. While we will provide results on comparative efficacy of the real and sham EA in treating CLBP, our primary focus is on mechanisms and predictors of the clinical outcomes.

The results of this mechanistic study could have future clinical care implications because they will inform on the potential contribution of pain regulatory processes (mediator) and expectation of benefit (moderator) to clinical outcome. Identification of mediators of clinical response could help guide selection of patients who are most likely to respond to EA. For example, those with deficits in a given mediator variable, such as those with temporal summation deficit may potentially have better response to acupuncture. Identification of moderators will help guide decisions about targets to enhance clinical outcome. For example, we can potentially augment clinical outcome from acupuncture by an intervention to enhance expectation of benefits.

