## Discussion

We have presented an ongoing clinical trial to evaluate the mechanisms of real vs sham EA for the treatment of CLBP. Our primary hypothesis is that the reduction in subjective rating of back pain bothersomeness in response to electroacupuncture will be mediated by reduction in ascending pain facilitation, which is measured by temporal summation. Clinically, if proven true, this hypothesis would allow us to utilize temporal summation as a predictor of clinical response to acupuncture treatments, i.e. those with amplified temporal summation would have increased likelihood to achieve symptom relief with acupuncture. We also hypothesize that the clinical effects of acupuncture will be moderated by the participant’s expectation of treatment benefits, i.e., the higher the expectation, the greater the degree of reduction in back pain bothersomeness. This hypothesis may allow us to potentially increase response to acupuncture treatments by augmenting a patient’s expectation of treatment benefits.

This study utilizes novel mechanistic markers involving an array of QST measures, and examines potential psychological moderators of clinical response to acupuncture, with expectation of benefits as a primary moderator. The study is expected to yield important knowledge on the pain regulatory pathways involved in both real (active) and sham (placebo) EA treatments. The majority of the existing studies on EA in CLBP focus on efficacy alone and are often limited by a heterogeneous sample population (i.e., patients with radicular back pain due to nerve root compression or those with acute and subacute back pain are included along with those with axial CLBP), lack of controls for non-specific effects, or small sample sizes. We designed the current study to minimize these limitations. To the best of our knowledge, this is the largest placebo-controlled study to date to evaluate EA as a treatment for back pain. The QST measures we selected will offer valuable insight into the pain regulatory mechanisms of real and sham EA. The study will also provide insight on psychological measures, such as expectation, catastrophizing and self-efficacy in managing pain, as moderators of treatment response to acupuncture. These measures have been studied extensively in the pain literature but are only beginning to gather attention in the field of acupuncture research.

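### Hypothesis 1b enters raw TS reduction without baseline TS and reads any significant TS-change term as mediation, so a baseline TS–pain link that weakens by week 4 can be declared mediation

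*Protocol article*

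**What the plan says.** Under Statistical methods, Hypothesis 1b, Planned analysis, the protocol article describes two mixed models for the weekly bothersomeness scores. The first has treatment assignment as predictor, and for it the article states: "The subject-specific intercept will be included to account for within-patient correlation". The second adds the mediator: "Treatment arm, reduction in TS from baseline to week 4, and their interaction will be the independent variables". The outcome of that second model is given as "with the longitudinally measured back pain bothersomeness scores as the independent variable", which must mean the dependent variable. Neither baseline TS nor baseline pain is listed.

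The decision rule follows: "A significant main effect for change in TS or an interaction between change in TS and treatment arm will be interpreted as evidence of mediation". No direction is required.

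Under Primary measures, TS is itself a difference of two ratings: "TS is estimated as the difference between the rating of the second pain from the first pulse from that of the most painful pulse". The mediator is the change in that difference. The plan for aim 3 reuses the same analysis with secondary measures, so change in conditioned pain modulation (CPM) is handled the same way.

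Two passages link a patient's TS level to response. The Discussion expects that "those with amplified temporal summation would have increased likelihood to achieve symptom relief with acupuncture", and Clinical impact says that "those with temporal summation deficit may potentially have better response to acupuncture".

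**The concern.** TS reduction is baseline TS minus week-4 TS, so it carries the baseline reading inside it. If people who start with high TS have a different pain course for any reason, part of that relation can appear in the TS-change coefficient. The stated rule then calls it mediation, even if what happens to TS during treatment has no bearing on pain.

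The Discussion names mediation by TS as the trial's primary hypothesis. A baseline characteristic that predicts pain is a different finding from a treatment mechanism, and the planned model cannot tell them apart.

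**Working it through.** **The plan's own figure.** The Sample size section says: "we have elected to power the study to detect a medium-sized effect (*d* = 0.56) with 50 subjects in each arm". With 50 per arm the noncentrality is 0.56 × √(50/2) = 2.80, and Φ(2.80 − 1.96) = Φ(0.84) = 0.80 (0.79 by the noncentral t). The figure reproduces, but it concerns hypothesis 1a. The article gives no error rate or power for hypothesis 1b.

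**Inputs.** From the article: 50 per arm, two-sided 0.05, an arm effect on TS of 0.56 SD, and the listed regressors. Assumed, because the article does not give them: ρ, the correlation of baseline with week-4 TS (0.3 to 0.7), and r, the correlation of baseline TS with pain (size 0.2 to 0.4).

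**Formulas (unit variances within arm).** Let r0 and r4 be the correlations of baseline and week-4 TS with pain.

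- Correlation of reduction with baseline: √((1 − ρ)/2).
- Planned (raw) slope: (r0 − r4) / (2(1 − ρ)).
- Slope with baseline TS added: −(r4 − ρ·r0) / (1 − ρ²).

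The raw slope is zero when r0 = r4. The adjusted slope is zero when r4 = ρ·r0. Neither model is right in both cases.

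**Case A: pain depends on the baseline reading only, so r4 = ρ·r.** The raw slope is r/2. Hand check at ρ = 0.5, r = 0.3: the correlation of reduction with pain is 0.3 × 0.50 = 0.15. The noncentrality is 0.15 × √100 / √(1 − 0.15²) = 1.52, and Φ(1.52 − 1.98) is about 0.32. Simulation (3,000 runs per cell, ordinary least squares on each person's mean pain, which matches a balanced random-intercept model for person-level terms) gives these false-positive rates for the TS-change main effect:

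| ρ | corr(reduction, baseline) | r = 0.2 | r = 0.3 | r = 0.4 |
|---|---|---|---|---|
| 0.3 | 0.59 | 21.5% | 43.3% | 65.6% |
| 0.5 | 0.50 | 17.6% | 31.8% | 50.9% |
| 0.7 | 0.39 | 12.4% | 21.3% | 33.1% |

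A repeat over both signs of r ran from 11% to 66%. Adding baseline TS brings the rate to 4–6%. Under the full rule (main effect or interaction) at ρ = 0.5, the planned model fires in 21.6%, 35.6% and 53.7%. With baseline TS added the figure is just under 10%, which two tests at 5% would give anyway (1 − 0.95² = 9.75%).

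**Case B: pain depends on a stable TS trait that both visits measure equally well, so r0 = r4.** With reliability 0.5 or 0.7 and r of 0.3 or 0.4, the planned main effect rejects in 4.7–5.6%. The adjusted model rejects in 25–71%. If the trait shows less at week 4 (loading 0.5 to 0.7 of baseline), both over-reject: planned 14–61%, adjusted 12–48%.

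**Direction.** If higher baseline TS goes with lower pain, virtually all of the planned model's Case A false positives point the hypothesised way (larger reduction, lower pain). If it goes with higher pain, at most 0.4% do. Where the two models are biased together, the formulas give their slopes opposite signs: in Case B with weaker week-4 loading, the raw slope has the sign of r and the adjusted slope the opposite sign.

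**Combined rule.** Requiring a significant main effect in the hypothesised direction in both the raw model and the model with baseline TS and baseline TS × arm gave at most about 3% false positives in every cell of both cases, for either sign of r.

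**The case against.** A reader might infer that any link between baseline TS and pain will be read as mediation. Case B shows that this goes too far: when both readings relate equally to pain, the planned test holds its level.

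A reader might also infer that baseline adjustment is the cure. It is not. With a noisily measured trait, week-4 TS acts as a second reading of the trait, and the adjusted model gives its own false signal. The Discussion acknowledges large variation between people in following and tolerating the sensory tests, so this case cannot be set aside.

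Nor do the Discussion and Clinical impact passages posit a baseline link that exists without mediation. Both present it as a consequence of mediation, should that be shown. They make a baseline link plausible, but they do not show that Case A applies.

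The sign also matters. If high TS goes with more pain, the false slope runs against the hypothesis and counts only because the rule sets no direction.

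Finally, a condensed article may leave covariates to the analysis plan. That has limited force here, because the article gives an explicit regressor list and an explicit decision rule. What stands is that the planned test is valid only if baseline and week-4 TS relate equally to pain, which the article neither states nor checks.

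**Conclusion.** The point holds in a conditional form. As written, the hypothesis 1b rule can declare mediation when TS change plays no part, if baseline TS relates to pain more strongly than week-4 TS does. The rate is about 11–66% for the main effect in Case A, and about 5% if the two relate equally.

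The size rests on assumed values of ρ and r and on an assumed way in which pain depends on TS. The documents settle none of these, so no single error rate can be assigned to this trial. The correlation of reduction with baseline needs only equal variances and a value for ρ. The lack of a direction in the rule is a plain feature of the text.

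**What to change.** Keep the planned second model and add a version with baseline TS and baseline TS × arm. State that mediation will be claimed only if the TS-change main effect is significant in the hypothesised direction (larger TS reduction, lower bothersomeness) in both versions. Code arm symmetrically so that this main effect is the average over arms. Report both models whatever they show, with the interaction as supporting information, and name the bothersomeness scores as the dependent variable. Apply the same rule to CPM in aim 3, with the direction stated for CPM. Settle this before unblinding.

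The cost is a sentence or two, two degrees of freedom, and a stricter criterion with somewhat less power. No new data are needed, because the per-protocol set already requires the baseline assessment.

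One limit should be stated. If week-4 TS is more strongly and positively tied to pain than baseline TS for reasons other than TS change, both slopes are negative by the formulas above, and the combined rule does not protect.
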